*** Reference - DMID Pediatric Toxicity Tables, May 2001, Drug Fever (Rectal)**

**** Reference – The Harriet Lane Handbook, 15th edition, 2000**

**† Reference – WHO Toxicity Grading Scale for Determining the Severity of Adverse Events**

**APPENDIX 2c :** **Guidelines for grading physical examination findings (cont.)**

|  | **Grade 1**  **MILD** | **Grade 2**  **MODERATE** | **Grade 3**  **SEVERE** | **Grade 4**  **LIFE-THREATENING** |
| --- | --- | --- | --- | --- |
| **Hearing** | *< 4 years: N/A*  > 4 years: Decreased hearing in one ear | *< 4 years: N/A*  > 4 years: Decreased hearing in both ears or severe impairment in one ear | *< 4 years: Any evidence of hearing impairment*  > 4 years: Severe impairment in both ears | N/A |
| **Tablet test** | Difficulty grasping tablet but able to pick up | Unable to pick up tablet without dropping | Unable to grasp tablet | N/A |
| **Clinical symptoms/sign** *(not otherwise specified)* | No therapy; monitor condition | May require minimal intervention and monitoring | Requires medical care and possible hospitalization | Requires active medical intervention, hospitalization, or hospice care |

**APPENDIX 2d :**

**Guidelines for grading splenic enlargement.**

Hackett splenic score (score from 0 to 5)

0 = spleen not palpable even on deep inspiration

1= spleen palpable on deep inspiration

2 = spleen palpable on normal inspiration, but not beyond a horizontal line half way between the costal margin and umbilicus, measured in a line dropped vertically from the left nipple

3 = spleen extending below this line, but not below a line running horizontally through the umbilicus

4 = spleen extending below this line, but not below a horizontal line half way between the umbilicus and pubic symphysis

5 = spleen extending below this line.

**APPENDIX 3**

**GUIDELINES FOR GRADING LABORATORY RESULTS: paediatric toxicity tables (greater than 3 months of age)**

|  | **Grade 1**  **MILD** | **Grade 2**  **MODERATE** | **Grade 3**  **SEVERE** | **Grade 4**  **LIFE-THREATENING** |
| --- | --- | --- | --- | --- |
| **Absolute neutrophil count *(/****mm3****)*** | 750 –1200 | 400 –749 | 250 –399 | <250 |
| **Hemoglobin**  ***(****g/dL)*  *age >3months and < 2 years* | 9.0 – 9.9 | 7.0 – 8.9 | <7.0 | Cardiac failure secondary to anemia |
| **Hemoglobin**  ***(****g/dL)*  *age >2 years* | 10 –10.9 | 7.0 –9.9 | <7.0 | Cardiac failure secondary to anemia |
| **Platelets *(/****mm3****)*** | N/A | 50,000 –75,000 | 25,000 –49,999 | <25,000 |
| **ALT *(U/L)*** | 1.1-4.9 x ULN | 5.0-9.9 x ULN | 10.0-15.0 x ULN | >15.0 x ULN |
| **AST *(U/L)*** | 1.1-4.9 x ULN | 5.0-9.9 x ULN | 10.0-15.0 x ULN | >15.0 x ULN |
| **Bilirubin** | 1.1-1.9 x ULN | 2-2.9 x ULN | 3.0-7.5 x ULN | >7.5 x ULN |
| **Creatinine**  3 months to 2 years of age | 0.6–0.8 x ULN | 0.9–1.1 x ULN | 1.2–1.5 x ULN | >1.5 x ULN |
| 2 to 12years of age | 0.7–1.0 x ULN | 1.1–1.6 x ULN | 1.7–2.0 x ULN | >2.0 x ULN |
| *Age>12 years* | *1.0–1.7 x ULN* | *1.8–2.4 x ULN* | *2.5–3.5 x ULN* | *>3.5 x ULN* |
| **Laboratory values**  *(not otherwise specified)* | Abnormal but requiring no immediate intervention; follow | Sufficiently abnormal to require evaluation as to causality and perhaps mild therapeutic intervention | Sufficiently severe to require evaluation and treatment | Life-threatening severity; requires immediate evaluation, treatment, and usually hospitalization |

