### Biological tolerability

- Haematology and biochemistry will be routinely performed on days 0, 7, and 28. Haematology and biochemistry will be repeated on Day 14 and 42 if results are abnormal on Day 7 and Day 28 respectively. Haematology and biochemistry may be performed on any other day if the clinician feels results are necessary for patient management. An additional haemoglobin evaluation will be performed on day 3 from blood collected by a fingerprick and read using a portable spectrophotometer (Haemacue). Blood samples for haematology and biochemistry will be collected from patients by venipuncture. About 2 mls of blood will be drawn from each patient for biochemistry/haematology during these visits. Additional venipunctures will be performed, as appropriate, for follow-up of adverse events.

Laboratory analyses are described in Appendix 6

- Haematological parameters: haemoglobin, platelets, leukocytes, neutrophils.These parameters will be measured by a complete blood count and assay of haemoglobin and measurements shall be done by a haematology coulter
- Biochemical parameters: blood creatinine, total bilirubin, ALT. These parameters will be measured according to the enzyme assay methods for each parameter.

Note: Any abnormal laboratory (at least grade 3) value will be immediately rechecked, in case of confirmation all investigations to know the reason will be performed and the patient will be followed until normalization. The possible withdrawal of the patient from the cohort will be taken by the investigator.

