# Patient safety

## Safety instructions

Safety and tolerability of the treatments will be evaluated by recording Adverse Events (AEs) and grading laboratory and vital signs evaluations. A severity grading scale, based on toxicity grading scales developed by the WHO and the National Institutes of Health, Division of Microbiology and Infectious Diseases, will be used to grade severity of all symptoms, physical exam findings, and haemoglobin results (see Appendix 2 and 3).

All laboratories abnormalities on D28 (ref: Appendix 3)

- Grade 2 or more for biological data
- Clinically significant abnormality (whatever the grade)

have to be followed until resolution or progression has to be stabilized.

For each malaria episode, follow-up for safety will be conducted during the scheduled malaria follow-up visits, and at any unscheduled visit. Follow-up for adverse events reported during a given malaria episode will continue until the patient is re-treated with study medications, or the study ends. If an AE is on going at the time of inclusion for a new malaria episode this AE will be recorded as a concomitant disease at D0 (the AE number recorded at the episode where this AE occurred will be specified to link them). At each episode a new cycle of adverse event assessment and reporting will begin according to the definitions of AE and SAE. Each AE will be considered as one until it has recovered.

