#### Laboratory variables analysis

Biological parameters will be summarized by group of treatment and overall at each time of measurement.

All abnormal variables will be graded and each parameter will be counted by grade.

The number of patients with abnormal data will be compared by grade between each treatment group and over the 2 years of follow-up

Transition tables will be provided between D0, D7 and D28 in order to assess the evolution of these parameters classified as normal/abnormal and by grade according to the laboratory ranges.

Absolute and relative changes to the baseline will be computed for each parameter for each attack. The evolution between D0 and D7 and D0 and D28 will be analyzed for each attack

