**2. Biochemical analyses**

The following biochemical parameters will be analysed: hepatic enzymes (ALT), total bilirubine, blood creatinine, and blood glucose. In the event of abnormal values, a control sample will be performed.

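### Hepatic events of special interest under section 11.8 can miss the ALT >10 ULN entry to the Appendix 5b guideline they are sent to; the ULN behind the Appendix 3 creatinine grades also needs stating

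*Protocol*

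**What the plan says.** **Hepatic AESI.** Section 11.8 sets two alternative limits: ALT above 8 x ULN, or ALT above 3 x ULN with total bilirubin above 2 x ULN. Either must reach the sponsor within one working day, and management is referred to Appendix 5. The readable part of Appendix 5b starts from a single box, ALT above 10 ULN. After a confirmatory repeat it calls for stopping the product, a search for other causes with serology, freezing of serum, and liver tests every 3 days in the first week, then weekly. It also says hospitalisation should be considered at ALT of 10 ULN or more, or with jaundice, a coagulation disorder or encephalopathy. Section 11.3 uses ALT of 10 ULN or more as an example of a serious event.

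**Other rules that reach the same children.** Appendix 6 states: "In the event of abnormal values, a control sample will be performed". Section 10.2.2 states: "Haematology and biochemistry will be repeated on Day 14 and 42 if results are abnormal on Day 7 and Day 28 respectively", and also: "Any abnormal laboratory (at least grade 3) value will be immediately rechecked". Section 11.1 requires D28 abnormalities of "Grade 2 or more for biological data" to be followed.

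**Creatinine.** Appendix 3 gives grade 1 for the youngest children as "3 months to 2 years of age | 0.6–0.8 x ULN", and for ages 2 to 12 as 0.7 to 1.0 x ULN. Section 14.5.4.2 says "All abnormal variables will be graded and each parameter will be counted by grade", with transition tables "classified as normal/abnormal and by grade according to the laboratory ranges".

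**The concern.** A limit that defines an event and the limit that opens its management guideline should agree. For neutropenia they do: both 11.8 and Appendix 5a use fewer than 400/mm3. For the liver they do not. A child can be an AESI, be referred to Appendix 5b, and fail its entry condition.

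Within one attack little is lost, because dosing ends on D2 and the first routine biochemistry after dosing is on D7. The stake is re-treatment. The assigned drug is given again for attacks from D14. The exclusion for hepatic impairment under amodiaquine appears only among the initial-enrolment criteria (8.3.1). The readable per-attack criteria contain no specific liver limit. For a child in the gap, whether to stop or to re-treat is left to the investigator (12.1.1, 12.3).

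The creatinine rows raise a smaller question. If ULN means the laboratory's age-specific limit, a child can be normal by range and still carry a grade in the same table.

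**Working it through.** **Hepatic gap.** Inputs, all in multiples of ULN:

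- AESI (11.8): ALT > 8, or (ALT > 3 and bilirubin > 2).
- Entry to Appendix 5b: ALT > 10.
- Gap = AESI and ALT ≤ 10. This is ALT > 8 to 10 at any bilirubin, plus ALT > 3 to 10 with bilirubin > 2.

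Example values:

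| ALT | Bilirubin | AESI (11.8) | Enters 5b | SAE example (11.3) |
|---|---|---|---|---|
| 3.5 | 1 | no | no | no |
| 3.5 | 2.5 | yes | no | no |
| 5 | 2.5 | yes | no | no |
| 7.5 | 1 | no | no | no |
| 8.5 | 1 | yes | no | no |
| 9.5 | 1 | yes | no | no |
| 10 | 1 | yes | no | yes |
| 10.5 | 1 | yes | yes | yes |

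At exactly 10 x ULN a child meets the AESI definition, the SAE example and the 5b hospitalisation condition, but not the 5b entry.

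**What still covers the gap.** Under Appendix 3, ALT 5.0 to 9.9 is grade 2 and 10.0 is grade 3; bilirubin 2 to 2.9 is grade 2 and 3.0 or more is at least grade 3. Every combination in the gap is therefore at least grade 2 on one parameter.

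- The control sample in Appendix 6 applies to any abnormal value, so it covers the whole gap.
- The grade 3 recheck in 10.2.2 reaches only ALT of 10.0 or bilirubin of 3.0 or more within the gap.
- For an event found on D7, the scheduled liver tests are the control sample, D14, D28, and D42 if D28 is abnormal. Appendix 5b would give tests every 3 days for a week, then weekly until normal or for at least 3 months.

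**Timing.** Re-treatment is possible from D14: 14 − 7 = 7 days after the D7 sample.

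**Creatinine.** The oldest possible age is 59 + 24 = 83 months, so only the two rows under 12 years apply. In steps of 0.1 x ULN:

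- Under 2 years, graded at or below 1.0: 0.6, 0.7 and 0.8 (grade 1), 0.9 and 1.0 (grade 2). That is five values; grade 3 starts at 1.2.
- 2 to 12 years, graded at or below 1.0: 0.7, 0.8, 0.9 and 1.0 (grade 1). That is four values; grade 2 starts at 1.1 and grade 3 at 1.7.
- ALT, AST and bilirubin: none, since grading starts at 1.1.

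There are three ways to read this:

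1. If ULN is age-specific, values within range are graded. Under 2 years, 0.9 to 1.0 on D28 is grade 2 and literally meets the follow-up rule.
2. If only out-of-range values are graded, grade 1 is empty to one decimal in both rows, and 1.1 is already grade 2.
3. If one common ULN is meant, which the lower bounds rising with age (0.6, 0.7, then 1.0 over 12 years) would fit, there need be no conflict, but the protocol does not say so or give its value.

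**The case against.** The best defence on the liver is that Appendix 5b is a flow chart flattened in reading, so a branch may be lost. Its own text hints at this: once entry requires ALT above 10 ULN, the hospitalisation condition of 10 ULN or more is always met and its other qualifiers add nothing. That fits a missing lower entry, but it equally fits an entry limit set too high. Both branches of the neutropenia chart survived reading. A lost branch is possible but not shown. It is also fair that a site following 11.8 would probably open 5b for these children anyway; that leaves the wording inconsistent but softens the effect.

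A reader might infer that children in the gap go unmonitored. The documents do not support that. They are reported within one working day, given a control sample, repeated on D14 or D42 where D7 or D28 is abnormal, and followed. Biochemistry is also taken at D0 of each attack. A general exclusion for severe concurrent illness applies at each attack, the copy available of that list breaks off in its last item, and the investigator may stop treatment or end cohort participation.

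A reader might also infer that the creatinine rows are an error. That cannot be decided here. The table is attributed to an external paediatric toxicity scale, the rows could rest on one common ULN, and 11.8 does expand the abbreviation ULN. The effect is limited as well: 14.5.4.2 grades abnormal values, the D28 rule is headed "All laboratories abnormalities on D28 (ref: Appendix 3"), and the grade 3 recheck is not triggered at or below ULN. Under 11.7 a laboratory value becomes an adverse event only if medically relevant.

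**Conclusion.** The hepatic mismatch stands on the readable text, assuming that no entry branch of Appendix 5b was lost. Its extent is ALT above 8 to 10 x ULN at any bilirubin, and ALT above 3 to 10 x ULN with bilirubin above 2 x ULN. How many children would fall there cannot be derived from the protocol. What is missing for them is the 5b package, not reporting, retesting or follow-up, and the consequence lies mainly in re-treatment with the same drug from D14.

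The creatinine point is subsidiary. As printed, the rows conflict with classification by laboratory range if ULN is the age-specific limit; otherwise what remains is an unstated reference limit.

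Neither part touches the primary endpoint, and nothing here shows bias between the arms. Severity is minor.

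**What to change.** Set the Appendix 5b entry to the 11.8 criteria (ALT > 8 x ULN, or ALT > 3 x ULN with total bilirubin > 2 x ULN). Keep ALT ≥ 10 ULN as the limit for considering hospitalisation, where it then does real work. In Appendix 3, state which ULN the creatinine rows use and its value, or restate the rows so that nothing within the age-specific normal range is graded.

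This corrects one entry limit and one table, and should be done before laboratory data are graded. The price is a few more hepatic work-ups and some children who may not be re-treated with their assigned drug.

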**Reference – DMID Pediatric Toxicity Tables, May 2001**

**APPENDIX 4**

**Criteria for Severe Malaria/Danger Signs (WHO, 2000)**

**Severe Malaria**

- prostration
- Unarousable coma *(if after convulsion, > 30 min)*
- Repeated convulsions *(> 2 within 24 h)*
  - Respiratory distress *(laboured breathing at rest)*
  - circulatory collapse
  - pulmonary oedema (radiological)
  - abnormal bleeding
  - jaundice
  - haemoglobinurea
  - Severe anaemia *(Hb < 5.0 g/dL)*
  - hypoglycemia
  - acidosis
  - hyperlactataemia
  - hyperparasitemia
  - renal impairment

**Danger Signs**

- Recent convulsions *(>1 within 24 h)*
- Altered consciousness  *(confusion)*
- Lethargy
  - Unable to drink or breast feed
  - Vomiting everything
  - Unable to stand/sit due to weakness

**APPENDIX 5 a**

*.*

**NEUTROPENIA**

| Neutrophils < 400/mm3 |
| --- |

| Repeat immediately a full blood count |
| --- |

| Neutrophils < 400/mm3 confirmed  with signs of infection |  | Neutrophils < 400/mm3 confirmed  with no sign of infection |
| --- | --- | --- |

| 1. DISCONTINUE Investigational Product, hospitalization should be considered. |  | 1. DISCONTINUE Investigational Product |
| --- | --- | --- |
| 1. PERFORM biological investigations for infection |  | 1. INVESTIGATE for etiology |

in both situations

| 1. INFORM the sponsor |
| --- |
| 1. INVESTIGATE previous treatments, particularly long-term, even a long time ago, exposure to toxic agents, e.g. benzene, X-rays, etc. |
| 1. PERFORM and collect the following investigations (results):  - RBC and platelet counts - Serology: EBV, (HIV), mumps, measles, rubella |
| 1. DECISION for potential bone marrow aspiration: to be taken in specialized unit |
| 1. FREEZE serum (5 mL x 2) on Day 1 (cessation of Investigational Product) and Day 5 (For further investigations). |
| 1. MONITOR the leukocyte and neutrophil counts 3 times per week for at least one week, then twice a month until it returns to normal, |

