## Inclusion criteria

### Specific inclusion criteria for initial enrollment

- Male and female children 6 to 59 months
- Confirmed mono infection with *Plasmodium falciparum*, with parasite density ≥ 2000 asexual forms per µl of blood
- Signed (or thumb-printed whenever parents/guardians are illiterate) informed consent by the parents or guardians (informed consent will be asked only at recruitment and will cover the whole period of the study, including subsequent follow up).
- Parents’ or guardians’ willingness and ability to comply with the study protocol for the duration of the trial.

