### Inclusion criteria for each attack (except the failures)

- Body weight ≥ 5 kg
- Able to be treated by oral route
- Fever (axillary temperature ≥ 37.5 degrees Celsius) at D0 or history of fever within the previous 24 hours (this criteria is not required in case of late failure after D14 in the previous attack)
- confirmed *Plasmodium falciparum* infection with positive parasitemia
- Haemoglobin value ≥ 5.0 g/dl;
- Agreement to comply with the study protocol

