**APPENDIX 5 b**

**INCREASE IN ALANINE AMINOTRANSFERASES**

| Increase in  ALT (SGPT) |
| --- |

| > 10 ULN |
| --- |

| Repeat immediately the count  if confirmed |
| --- |

| 1. DISCONTINUE administration of the Investigational Product 2. HOSPITALIZATION should be considered if ALT ≥ 10 ULN and/or jaundice or coagulation disorder (PT <50% with factor V <50%) or signs of hepatic encephalopathy 3. INFORM the sponsor 4. INTERVIEW patient again about consumption of alcohol, drugs and herbals received *before* and *during* the trial and possible contamination by HAV, HBc or HCV virus in the last six months (blood or blood product transfusion, intravenous drug addiction) 5. INVESTIGATE for other etiology | 1. PERFORM the following examinations :  - Complete blood count and LFTs - Serum creatinine - Anti-HIV IgM, anti HBc IgM, anti-HCV IgM, anti-CMV IgM - Specific serologic markers of recent infection with ***** EBV, herpes viruses and toxoplasma (depending on the clinical context) ***** hepatobiliary ultrasonography  1. FREEZE serum (5 mL x 2) 2. MONITOR LFTs (including aminotransferases) every 3 days for the first week then once weekly until return to normal or for at least 3 months |
| --- | --- |

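### Appendix 5 orders an ambiguous stored-serum volume not fitted to children from 5 kg, and the serology list in 5b does not match its own interview line on hepatitis A

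*Protocol*

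**What the plan says.** Section 11.8 defines the special-interest events (low neutrophils, raised ALT with or without raised bilirubin) and refers the site to Appendix 5 for their management. Section 26 makes the appendices part of the protocol.

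- **Stored serum, Appendix 5a (neutropenia):** "FREEZE serum (5 mL x 2) on Day 1 (cessation of Investigational Product) and Day 5".
- **Stored serum, Appendix 5b (ALT increase):** "FREEZE serum (5 mL x 2"), with no day given.
- **Population, sections 8.2.1 and 8.2.2:** "Male and female children 6 to 59 months"; at each attack "Body weight ≥ 5 kg" and "Haemoglobin value ≥ 5.0 g/dl".
- **Routine sampling, section 10.2.2:** "About 2 mls of blood will be drawn from each patient for biochemistry/haematology during these visits". The same section allows additional venipunctures to follow up adverse events, with no volume and no limit by weight.
- **Interview line, Appendix 5b:** staff ask about "possible contamination by HAV, HBc or HCV virus in the last six months".
- **Serology list, Appendix 5b:** "Anti-HIV IgM, anti HBc IgM, anti-HCV IgM, anti-CMV IgM".

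**The concern.** Two things in Appendix 5 look as though they were not checked against this trial.

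The first is the stored serum. The instruction is in millilitres of serum, which takes a larger volume of blood to obtain. It comes on top of the other tests ordered in the same work-up, and nothing scales it to a child who may weigh 5 kg and be severely anaemic. It is also unclear. In 5a the factor of two may mean two 5 mL portions on each of two days, or one 5 mL portion on each day. Two readers of the same page could differ by a factor of two in what they take from the child.

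The second is the viral work-up after an ALT rise. The interview line and the serology list share hepatitis B core and hepatitis C, but the interview has hepatitis A where the list has HIV. A cause the site is told to ask about is not among the tests it is told to run. An ALT rise with an undetected viral cause might then be judged possibly related to the study drug.

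**Working it through.** **Inputs from the protocol.** Minimum weight 5 kg and haemoglobin floor 5.0 g/dl (8.2.2); routine draw about 2 mL (10.2.2); stored serum 5 mL times 2, on Day 1 and Day 5 in 5a and with no day in 5b.

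**Assumptions not in the protocol.** Haematocrit 0.15 to 0.40, the low end representing an anaemic child; blood volume 70 to 80 mL/kg; no loss on separation. Blood volume at 5 kg is then 5 × 70 = 350 mL to 5 × 80 = 400 mL.

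**Formulas.** Whole blood needed = serum ÷ (1 − haematocrit). Share = whole blood ÷ blood volume. The low end of each range pairs haematocrit 0.15 with 400 mL; the high end pairs 0.40 with 350 mL.

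| Reading | Whole blood | Share at 5 kg |
| --- | --- | --- |
| Routine draw, 2 mL of blood | 2 mL | 2/400 = 0.5% to 2/350 = 0.6% |
| 5 mL serum (5a, one portion per day; figure for one day) | 5/0.85 = 5.9 to 5/0.60 = 8.3 mL | 1.5% to 2.4% |
| 10 mL serum (5b as two portions; 5a as two portions on one day, or one portion on each day in total) | 10/0.85 = 11.8 to 10/0.60 = 16.7 mL | 2.9% to 4.8% |
| 20 mL serum (5a, two portions on both days) | 20/0.85 = 23.5 to 20/0.60 = 33.3 mL | 5.9% to 9.5% |
| 10 mL, if the figures mean whole blood | 10 mL | 2.5% to 2.9% |
| 20 mL, if the figures mean whole blood | 20 mL | 5.0% to 5.7% |

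Against the routine draw, the smallest reading of all (5 mL of whole blood on one day) is 5/2 = 2.5 times. Ten mL of serum is 11.8/2 = 5.9 to 16.7/2 = 8.3 times.

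The shares fall with weight. For 10 mL of serum they are 1.6% to 2.6% at 9 kg and 0.8% to 1.3% at 18 kg. Anaemia works in two directions: it is the reason the volume matters, but a lower haematocrit also yields more serum per millilitre of blood, so the low end of each range applies to the most anaemic children.

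**Which reading of the factor of two?** 5b uses the same expression with no days attached, which favours two portions on one occasion. If 5a means the same, it asks for 10 mL of serum on each of two days. The text does not settle this.

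**Interview against serology in 5b.**

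| Virus | Interview line | Serology list |
| --- | --- | --- |
| Hepatitis A | yes | no |
| Hepatitis B core | yes | yes |
| Hepatitis C | yes | yes |
| HIV | no | yes |
| CMV | no | yes |

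The pattern would fit a slip of HIV for HAV, but the protocol does not show whether it is one.

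**The case against.** The strongest reply is that nothing here contradicts anything. The 2 mL figure describes scheduled safety visits, while Appendix 5 describes an exceptional work-up, and section 10.2.2 expressly allows more venipuncture for adverse events. That stands: a reader might infer a direct conflict between 10.2.2 and Appendix 5, and the protocol does not support one. What remains is an unscaled and unclear volume.

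A reader might also infer that small and often anaemic children would be bled heavily. The protocol gives no expected frequency of anaemia at these events or of the events themselves. The work-up starts only after a confirmed neutrophil count below 400/mm3 or a confirmed ALT above 10 times the upper limit. On the smallest serum reading the daily amount is 1.5% to 2.4% of blood volume at the lowest permitted weight, and less in heavier children.

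On hepatitis A, it is tempting to say the test would be omitted and the hepatic comparison distorted. But 5b also tells the site to look for other causes, which permits the test. Section 14.5.4.2 compares laboratory abnormalities by grade regardless of cause, and 14.5.4.1 tabulates all treatment-emergent events as well as the possibly related ones. Only the possibly related tables could shift.

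Some may call the appendix an adult template because it asks about alcohol and intravenous drug use. That is an inference. The mumps, measles and rubella serology in 5a and the questions on herbals and transfusion in 5b apply to children, and the protocol does not say where the text came from.

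Finally, Appendix 6 leaves sampling and storage detail to an operating manual that is not shown. It may clarify the instruction. But the volume is written into the protocol itself, and section 26 restricts changes made without an amendment, so the manual should not be relied on to alter it.

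**Conclusion.** The point holds as a minor one, in two parts. First, the stored-serum instruction in 5a and 5b is ambiguous and has not been fitted to children from 5 kg with haemoglobin down to 5.0 g/dl. It exceeds the routine draw by at least 2.5 times on every reading. At 5 kg the serum readings run from 1.5–2.4% of blood volume for a single 5 mL portion to 5.9–9.5% for the two-day maximum. The percentages rest on the assumed haematocrit and blood volume per kilogram; the ambiguity and the 2.5-fold minimum do not. Second, hepatitis A is asked about but not listed for testing in 5b, while HIV is listed but not asked about. That mismatch could affect how individual hepatic events are judged for relatedness.

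Neither part touches the primary endpoint, the sample size or the non-inferiority analysis.

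**What to change.** The sponsor should reconcile the stored-serum instruction in Appendix 5a and 5b with the entry weight and haemoglobin floor in section 8.2.2 and with the routine draw in section 10.2.2. The text should say what the factor of two means, whether the figure is serum or whole blood, and whether it applies per day or in total. The sponsor should also reconcile the 5b serology list with the 5b interview line on HIV and hepatitis A. Which volume, which tests and whether the sample is kept are clinical decisions for the sponsor and investigator; none is proposed here.

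The cost is appendix wording in an amendment, with the approvals that section 26 requires. It adds no procedure and leaves the statistical analysis unchanged.
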